### Description of comparator intervention

The physical activity programmes in the comparator intervention will be run by the LSPs at existing exercise hubs in community settings. The programmes were developed as part of Ireland’s national physical activity plan, ‘Get Ireland Active’ [28]. These programmes run nationally and their purpose is to encourage and support physical activity by facilitating access to a wide range of physical activity opportunities in local communities. For Move for Life, four existing LSP programmes were identified as suitable for inactive adults aged 45 + years. Two programmes are gender segregated: ‘Men on the Move’ and ‘Women on Wheels’, both are 12-week structured exercise classes involving general sport, physical activities and cycling. ‘Get Ireland Walking’ is an 8-week walking initiative for inactive men and women; ‘Go for Life’ is an 8-week structured exercise class that typically recruits older adults aged 65 years plus. For the purposes of the comparator intervention in this trial, these programmes will run in the usual way so that participants are exposed to a community-based structured physical activity programme. Participants in the intervention arm of the trial will have these programmes augmented by the Move for Life intervention.

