### Development of the intervention

Three hubs will be allocated to the MFL intervention arm. Documents relevant to the four LSP programmes to be augmented for MFL were examined. In 2018, a qualitative study, involving stakeholders in current community exercise programmes, was conducted to investigate factors that affect recruitment, retention and scalability of these programmes.

Using the sources outlined, the MFL intervention was designed on a foundation of theoretical, empirical and practical information. The intervention mapping approach was used to identify theory-based determinants and matching them with appropriate methods for change [29]. A toolkit in the form of a training manual has been developed to train MFL professional instructors in key behaviour change techniques, involving social support and group dynamic strategies along with behavioural skills, aimed to facilitate change and maintenance of physical activity over time. The MFL toolkit contains strategies and outcomes identified in the intervention mapping process. The process will be described in more detail in a separate paper. Social cognitive theory (SCT) [30] was the primary conceptual framework of the intervention because of its emphasis on self-efficacy and social support. Behavioural skills strategies to address outcome expectancy and self-efficacy determinants of behaviour were derived from previous SCT-based intervention work [31, 32] The Theory of Planned Behaviour [33], a second conceptual framework, guided the intervention design in terms of influencing participants’ attitudes and beliefs around physical activity. Self-determination theory (SDT) [34] was a third conceptual framework, using its focus on basic psychological needs for autonomy and relatedness to others to having a positive impact on desired behavioural outcomes [35]. A fourth conceptual framework, the model of group cohesion in exercise and sport [36], was employed, with particular emphasis on task cohesion (i.e. how well participants work together toward a common goal) and social cohesion (i.e. how much participants enjoy working with each other toward the goal) to develop strategies for the group to achieve its outcomes.

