## Outcomes

The primary outcome of the study is to investigate the feasibility of measuring MVPA. The acceptability and safety of the intervention and measurement methods will be investigated. The data will provide reliable estimates for sample size calculation for a future definitive trial. Secondary outcomes relate to data on recruitment, allocation, retention, attrition and attendance. Data will be collected on safety and adverse events will be recorded by the LSP tutor. Participant recruitment outcomes include demographic profile and the success of each of the recruitment strategies. Participant retention outcomes include the number, profile and reasons of participants that drop out. Data will be collected on the numbers who complete each part of the physical activity measures and questionnaires and who wear and return the activPAL devices. Questionnaires will enable the collection of data on healthcare resource use, out-of-pocket expenses and health-related quality of life. For each secondary outcome, the point estimate of effect will be reported, and precision will be presented with 95% confidence intervals. SPSS version 25 will be used for the statistical analyses. At specific time-points, immediately post intervention and 3 months post intervention, follow-up testing sessions will take place. The authors define ‘minimum thresholds’ in the context of the post intervention and 3-month follow up testing as the minimum proportion of participants that attend the testing sessions and provide reliable data.

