**Fig. 3 Fig3:**
[figure not shown]
Timeline for the Limerick hubs

Interviews of stakeholders involved in previous physical activity programmes were conducted between January and March in order to inform the intervention development. From January to April, the team has developed the intervention. The trial commences in May and 8 weeks before commencing, and recruitment strategies have been developed. Four weeks beforehand, information sessions will take place. The trial will commence with recruitment, enrolment and baseline testing in Limerick hubs in May until July and in Clare from August until October. Follow-up testing at 3 and 6 months will follow for the hubs in Limerick and Clare.

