The trial will have staggered commencement which is not unusual for a cluster feasibility trial but may have a seasonal effect. It is anticipated that the shorter daylight hours in Ireland from November to February could impact on the outcomes of hours of physical activity and sedentary time especially with regard to follow-up testing which will be in September for some and in mid-winter for later starters. Using freely accessible online data [41], the results will be correlated to the number of daylight hours.

The study will generate important data relating to recruitment and retention of participants; concealment of randomisation; and acceptability and appropriateness of intervention components, data collection and factors for analysis. The data will determine if a larger RCT is possible and will inform the research team of important considerations when planning a trial of larger magnitude.

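### The Discussion's follow-up calendar fits only the 3-month visit, and the stated daylight correlation, which accounts for neither visit nor county, mixes season with time since baseline

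*Protocol article*

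**What the plan says.** - The Discussion expects the short days from November to February to affect activity and sedentary time, above all at follow-up. It places "follow-up testing which will be in September for some and in mid-winter for later starters".
- Its one stated analysis of season is that, using online daylight data, "the results will be correlated to the number of daylight hours".
- The timeline text under Fig. 3 (Data collection) gives "recruitment, enrolment and baseline testing in Limerick hubs in May until July and in Clare from August until October", and adds: "Follow-up testing at 3 and 6 months will follow for the hubs in Limerick and Clare".
- Outcomes times the same two visits differently, as "immediately post intervention and 3 months post intervention". Under Description of comparator intervention, two programmes last 8 weeks; of the other two, "both are 12-week structured exercise classes".
- Development of the intervention describes the instructor toolkit as "aimed to facilitate change and maintenance of physical activity over time".
- Outcomes makes the feasibility of measuring MVPA the primary outcome. The Analysis plan treats all testing and modelling as exploratory.

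**The concern.** The Discussion identifies the seasonal threat but describes it as a matter of early against late starters. On the article's own dates the early starters also reach mid-winter, at 6 months instead of 3. Between the two follow-up visits the days shorten in Limerick and lengthen in Clare, so one pooled time course blends opposite seasonal trends.

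The proposed remedy does not deal with this. A correlation of results with daylight, as stated, has no term for visit or county. In Limerick the days shorten steadily from baseline to 6 months, so activity that fades once classes end and activity that falls because evenings are dark would produce much the same coefficient. At stake is the reading of preliminary MVPA and sedentary-time patterns: a reader could credit season with a waning programme effect, or the reverse, when planning the definitive trial.

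**Working it through.** **1. The calendar.** Inputs: the baseline windows and the 3- and 6-month visits from the timeline text.

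| County | Baseline | +3 months | +6 months |
|---|---|---|---|
| Limerick | May–July | August–October | November–January |
| Clare | August–October | November–January | February–April |

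The Discussion's contrast of September with mid-winter is reproduced in the 3-month column. It is not reproduced at 6 months, where the early starters are in mid-winter and the later starters are leaving it.

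Sensitivity to the Outcomes timing: a 12-week programme plus 3 months is close to 6 months, so nothing changes. An 8-week programme moves both visits about a month earlier. Limerick's become July–September and October–December; Clare's become October–December and January–March. Limerick's last visit still reaches early winter.

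**2. Daylight.** Assumptions: latitude 52.7 N, and mid-month day length with equal numbers starting each month. Hours from a standard day-length formula:

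| Start month | Baseline | 3 months | 6 months |
|---|---|---|---|
| Limerick: May / June / July | 15.7 / 16.8 / 16.4 | 14.8 / 12.8 / 10.7 | 8.8 / 7.7 / 8.1 |
| Limerick mean | 16.3 | 12.8 | 8.2 |
| Clare: August / September / October | 14.8 / 12.8 / 10.7 | 8.8 / 7.7 / 8.1 | 9.9 / 11.8 / 13.9 |
| Clare mean | 12.8 | 8.2 | 11.8 |

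From 3 to 6 months the change is 8.2 − 12.8 = −4.6 h in Limerick and 11.8 − 8.2 = +3.6 h in Clare.

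**3. Correlation of daylight with months since baseline**, r = Sxy / √(Sxx·Syy), with time centred at −3, 0 and 3:

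- Limerick: Sxy = 3 × (24.6 − 48.9) = −72.9; Sxx = 54; Syy = 108.6; r = −72.9 / 76.6 = −0.95.
- Clare: Sxy = 3 × (35.6 − 38.3) = −8.1; Sxx = 54; Syy = 52.1; r = −8.1 / 53.1 = −0.15 (−0.16 before rounding the hours).
- Pooled: Sxy = −81.0; Sxx = 108; Syy = 170.6; r = −81.0 / 135.7 = −0.60.

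Spreading baseline evenly over every day of each window, with 91 and 182 days added, gives about −0.94, −0.12 and −0.58. The Clare value is small and moves a little with the day-length formula and averaging (−0.12 to −0.16).

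**4. Can daylight and visit be separated?** Variance inflation for daylight = 1 / (1 − R²), where R² comes from regressing daylight on visit and county. Daily dates give R² = 0.474 and 1 / 0.526 = 1.9. Mid-month dates give 0.494 and 1 / 0.506 = 2.0. With visit alone, on mid-month dates, Limerick by itself gives 1 / (1 − 0.912) = 11.4 and Clare by itself 1 / (1 − 0.673) = 3.1. Using both counties makes separation workable, provided the daylight effect is the same in both.

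**5. Are arm comparisons within a county always available?** There are 8! / (3!·3!·2!) = 560 unrestricted allocations of eight hubs to 3, 3 and 2, with four hubs in each county. Every arm appears in both counties only when one county holds 1, 2 and 1 hubs of MFL, usual programme and true control and the other holds 2, 1 and 1, or the reverse. That is 2 × 12 × 12 = 288 allocations, or 51%. In the remaining 49% some arm lies wholly in one county. With the most even urban–rural split the figure is 56%. The Discussion stratifies by urban–rural only, so county is not balanced by design.

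**The case against.** A reader might infer that daylight and time since baseline cannot be told apart in this trial, and that change or maintenance of MVPA therefore cannot be read at all. The documents do not support that. The staggered start is what breaks the collinearity, and only Limerick taken alone is close to collinear. The trial also has usual-programme and true-control arms measured at the same visits, so hubs of one county share the season apart from differences in start date inside the window. No section plans to present within-arm change as a programme effect, and the phrase about maintenance describes the toolkit, not an estimand.

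Other points in the plan's favour stand. The Discussion does not say that early starters avoid winter, and its contrast is right for the 3-month visit. The timeline windows cover recruitment and enrolment as well as baseline testing, and the Limerick timeline figure is not shown, so exact test dates are assumed. The article does not call the correlation unadjusted or claim that it corrects an estimate. The Analysis plan allows exploratory regression, and covariates may be set out in an analysis plan that is not shown. No progression criterion uses change in MVPA.

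What remains is that the stated calendar is incomplete against the article's own dates, and that the one seasonal analysis the article commits to would, taken as stated, mix two explanations.

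**Conclusion.** The point holds in a limited form. The Discussion's calendar covers only the 3-month visit; both counties have a mid-winter visit, Limerick at 6 months and Clare at 3. Correlating results with daylight, with no account of visit or county, confounds season with follow-up time: strongly in Limerick (about −0.94), little in Clare (about −0.12) and moderately pooled (about −0.58). These figures rest on latitude 52.7 N and uniform baseline dates.

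The weakness lies in the stated analysis, not in the design: modelling both counties together separates the two at roughly double the variance for the daylight term. The damage is confined to that correlation and to uncontrolled within-arm change. Both are exploratory, and neither bears on the primary feasibility outcome or the decision to progress.

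**What to change.** 1. Correct the Discussion: on the stated dates, mid-winter testing falls at 6 months in Limerick and at 3 months in Clare. Note that visits timed from the end of an 8-week programme come about a month earlier.
2. Replace the plain correlation with an exploratory model of MVPA and of sedentary time that includes arm, visit, county (start block) and daylight hours in each participant's wear week. State the assumption of a common daylight effect.
3. Show results descriptively by arm, visit and county.
4. State that uncontrolled within-arm change will not be read as a programme or maintenance effect.

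The cost is wording and a few model terms, since hub county and wear dates come with the data. The daylight term will have wider intervals. Within-county contrasts should stay descriptive and cannot be the only reading free of season: four hubs serve three arms, so when all arms are present two of them rest on a single hub, and in about half of allocations some arm is missing from one county.

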## Data Availability

The datasets generated and/or analysed during the current study are not publically available due to variables in the data which could identify authors and location of hubs. Data generated after the trial has been completed and will be available from the corresponding author on reasonable request.

## Abbreviations

BCW: Behaviour change wheel
BMI: Body mass index
ICC: Intra-cluster coefficient
LSP: Local Sports Partnership
LSPs: Local Sports Partnerships
MFL: Move for Life
MVPA: Moderate to vigorous physical activity
MVPA: Moderate to vigorous physical activity
PA: Physical activity
PAGL: Promotes physical and mental health
RCT: Randomised controlled cluster trial
RCT: Randomised controlled trial
